### Secondary outcomes

Hypoglycaemia (any blood glucose concentration < 2.6 mmol/L in the first 48 h);Admission to NICU for hypoglycaemia;Hyperglycaemia (any blood glucose concentration > 10 mmol/L);Breastfeeding at discharge from hospital (full or exclusive);Received any formula prior to discharge from hospital;Formula feeding at 6 weeks of age;Cost of care until primary discharge home;Maternal satisfaction (via telephone questionnaire at 6 weeks);Neurosensory disability at 2 years’ corrected age (any of: legal blindness; sensorineural deafness requiring hearing aids; cerebral palsy; Bayley Scale of Infant Development Version III cognitive, language or motor score lower than one standard deviation below the mean).

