## Data analysis

The primary outcome of NICU admission will be analysed by logistic regression, stratifying by collaborating centre. Secondary analyses will adjust for potentially confounding variables: reason for risk of hypoglycaemia (infant of diabetic, late preterm, small or large), sex, gestational age, and mode of birth (vaginal vs caesarean section). Continuous data will be compared by Student’s *t* test, or the Mann–Whitney *U* test if the data are not normally distributed and cannot be converted to near-normality by simple transformation. Data with repeated points, such as blood glucose concentrations, will be compared using mixed model techniques, modelling the main effect of treatment group allocation, time and their interaction, with significant main effects and interactions tested using the method of Tukey. All tests will be two-tailed, with P < 0.05 considered significant. The data will be analysed on an intention-to-treat basis, and any baby who dies or for whom the primary outcome of NICU admission cannot be determined will be assigned the worst case outcome of NICU admission.

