### Economic evaluation

The cost-effectiveness of oral dextrose gel to prevent neonatal hypoglycaemia will be compared with usual care (no prophylaxis) within the period to discharge.

Intervention costs: A per-baby cost of dextrose gel will be based on the cost of the gel syringes and dispensing costs. For the no prophylaxis option, a zero intervention cost will be assumed.

Other Hospital Costs: Resource utilisation will be obtained from a clinical record form identifying both length of stay (LOS) and relevant Diagnostic Related Group (DRG) code for the mother, plus any subsequent operative procedure (DRG), respiratory problem requiring treatment (DRG), and NICU admission for the baby (plus LOS). Costs will be assessed using New Zealand Ministry of Health cost weights and purchase unit prices. For the no prophylaxis option, the costs from the placebo gel arm will be used.

Cost-effectiveness will be assessed using incremental cost-effectiveness ratios (ICERs) formed in terms of an incremental cost per case of hypoglycaemia avoided. Uncertainty in these figures will be assessed using non-parametric bootstrapping (sampling with replacement) to form a distribution for the ICER, potentially including corrections for any differences in the composition of the trial arms in any confounding factors. This analysis will be presented using cost-effectiveness acceptability curves that identify the likelihood of each option being cost-effective for different values attached to reducing a case of hypoglycaemia.

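### The cost-of-care outcome is not exempted from the t-test or Mann-Whitney rule, so the plan does not fix that arithmetic mean costs are compared

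*Protocol article*

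**What the plan says.** The protocol article deals with cost in three places.

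- Secondary outcomes lists "Cost of care until primary discharge home" as an outcome in its own right.
- Data analysis gives one rule for continuous data without repeated measurements: "Continuous data will be compared by Student’s" t test, or Mann-Whitney U "if the data are not normally distributed and cannot be converted to near-normality by simple transformation". No outcome is exempted, and a two-sided 5% level applies to all tests.
- Economic evaluation builds the costs. For the gel, "A per-baby cost of dextrose gel will be based on the cost of the gel syringes and dispensing costs". For the comparator, "For the no prophylaxis option, a zero intervention cost will be assumed", and "For the no prophylaxis option, the costs from the placebo gel arm will be used". On pricing, "Costs will be assessed using New Zealand Ministry of Health cost weights and purchase unit prices". On precision, "Uncertainty in these figures will be assessed using non-parametric bootstrapping (sampling with replacement) to form a distribution for the ICER". Acceptability curves follow.

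The Economic evaluation section names no estimate, test or interval for the cost difference alone. Neither section says which of them governs the secondary outcome.

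**The concern.** The Aim section wants to know whether prophylaxis reduces costs, and the numerator of the cost-effectiveness ratio is a difference in mean cost. Costs in which roughly one baby in ten has a NICU stay are likely to have a long right tail, and this is where the stated rule moves away from a t test on raw cost. Mann-Whitney then compares ranks, and a t test on logs compares geometric means. Neither answers the question about mean cost.

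The cost structure makes this more than a technicality. On the protocol's costing, every dextrose baby carries a small extra amount, while the designed benefit is a 4-point fall in NICU admission. Ranks respond to the small amount on everyone and give little weight to the large saving in a few. At stake is a missed saving or, in some cost layouts, a p-value for cost that disagrees with the economic evaluation of the same babies.

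**Working it through.** **Inputs from the protocol.** From Power and sample size: NICU admission 10% v 6%, 1,014 babies per arm, two-sided alpha 0.05, power 90%. From Economic evaluation: gel cost on the dextrose arm, zero intervention cost on the comparator.

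**The plan's own figure.** The two-proportion formula with continuity correction gives 1,014 per arm (965 without it), so 2 × 1,014 = 2,028. Then 2,028 × 1.05 = 2,129.4, which matches the stated 2,129. The rates and arm size used below are therefore the plan's own.

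**Assumptions, because the protocol gives no amounts.** Mean base cost 3,000 units, gel 5 to 100 per baby, NICU cost gamma-distributed with mean 3,000 or 10,000. Dextrose affects cost only through NICU admission.

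**Step 1: mean difference.** Dextrose minus comparator = gel − (0.10 − 0.06) × mean NICU cost. With gel 100 and NICU 3,000 this is 100 − 120 = −20. With gel 5 and NICU 10,000 it is 5 − 400 = −395. Dextrose is cheaper on average in every scenario.

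**Step 2: fully tied base costs.** If all non-admitted babies share one base cost, any gel cost above zero (and small beside a NICU stay) gives

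P(dextrose baby ranks dearer) = 0.94 × 0.90 + 0.06 × 0.90 + 0.5 × 0.06 × 0.10 = 0.846 + 0.054 + 0.003 = 0.903.

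The ranks say dearer while the mean says cheaper, whatever the gel price.

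**Step 3: untied base costs, no gel cost.** If admitted babies rank above all others, the same sum is 0.5 × 0.846 + 0.054 + 0.003 = 0.480, which is 0.020 below one half. The standard error is √[2,029 / (12 × 1,014²)] = 0.0128, so z = 0.020 / 0.0128 ≈ 1.56 and power ≈ Φ(1.56 − 1.96) ≈ 34%. Any gel cost, or overlap between admitted and non-admitted costs, lowers this. Under these assumptions a rank test on untied costs finds the saving about one time in three at best.

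**Step 4: simulation.** 1,014 per arm, 400 trials per scenario. Ranges run over both NICU costs. The t test is on raw cost and stands in for a comparison of means.

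| Base cost of non-admitted babies | Gel | Mann-Whitney: dextrose significantly dearer | Mann-Whitney: significantly cheaper | t test: significantly cheaper |
|---|---|---|---|---|
| Identical | 5–100 | 100% | 0% | 7–80% |
| Banded: 2 DRG levels × 4 lengths of stay | 5–100 | 95–99% | 0% | 4–66% |
| Continuous, SD 300 | 5–20 | 0–1% | 4–23% | 57–77% |
| Continuous, SD 300 | 50 | 36–40% | 0% | 34–59% |
| Continuous, SD 300 | 100 | 99% | 0% | 6–51% |
| Continuous, SD 1,000–2,000 | 5–20 | 0% | 12–31% | 17–69% |
| Continuous, SD 1,000–2,000 | 50 | 0–2% | 3–11% | 11–59% |
| Continuous, SD 1,000–2,000 | 100 | 3–14% | 0–4% | 4–49% |

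In the banded layout, the rank test was significant for dearer while the sample mean was cheaper in 60 to 97% of trials. For SD 1,000–2,000 with NICU cost 10,000 alone, Mann-Whitney found the saving in 1 to 31% and the t test in 44 to 69%.

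**Step 5: a second layout.** With four DRG cost levels and no spread within a level, the rank test was wrong in direction in 100% of trials. With 5 to 20% spread within a level this fell to 0 to 1% at gel 2 to 10, and to at most 8% at gel 50. At gel 2 to 10, Mann-Whitney then found the saving in 8 to 23% and a comparison of means in 26 to 52%.

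**The case against.** The strongest reply is that cost has its own section. The Data analysis sentence is generic and never mentions cost, whereas Economic evaluation covers the construction, comparator, uncertainty and presentation of costs. A specific section usually governs a general one, and its bootstrap replicates already contain the mean cost difference. The one-sided gel cost also appears only there, as an input to the ratio, and no section plans to put that cost through a rank test. This stands to the extent that the protocol does not positively assign cost to the rank test. It does not remove the gap: the section never says that it replaces the general rule for the listed outcome, and a ratio per case of hypoglycaemia avoided is not a comparison of costs.

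A reader might infer that the trial would report dextrose as significantly dearer when it is cheaper. The documents do not support that as a prediction. It needs heavily tied costs, or a gel cost that is large beside the spread of costs, and it needs gel cost to be counted in the outcome. The protocol gives no amounts, spread or banding. It also records lengths of stay and procedures, which may break up ties. Fewer hypoglycaemic episodes could lower costs in babies never admitted, which would favour dextrose in the ranks, and the simulation leaves this out.

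Nor is it certain that Mann-Whitney would be reached, since a t test and then a transformation come first. A transformed scale would still not compare arithmetic means.

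**Conclusion.** The point holds as a gap in coordination between two sections, and it is minor. The general rule does not exempt cost of care, and the Economic evaluation section does not say how the cost difference is compared. Followed literally, the text allows a test that does not address mean cost.

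Under the assumed costs, the usual consequence with well-spread costs and cheap gel is lost power: 12 to 31% for Mann-Whitney against 17 to 69% for a comparison of means. A reversal of direction is possible, and near certain in the tied layouts, but rare with well-spread costs and a small gel cost. How often it would happen in this trial cannot be read from the protocol.

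The primary outcome, the sample size and the bootstrapped ratio are unaffected. A reader might also extend the criticism to the rule for other continuous outcomes, but no error is shown there.

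**What to change.** Add one sentence to Data analysis or Economic evaluation: cost of care to primary discharge is exempt from the normality rule and is compared as the difference in arithmetic mean cost per baby, with a bootstrap confidence interval from the same replicates as the cost-effectiveness ratio. Leave the rule for other continuous outcomes as it is.

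The bootstrap is already planned, so the cost is the sentence itself. If the sponsor always meant the Economic evaluation section to govern cost, the sentence only records that.

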### Power and sample size

Based on data from Auckland City Hospital and Waikato Hospital, 10 % of at-risk babies will require admission to NICU. A trial of 2,129 babies (1,014 in each arm, with continuity correction and allowing for 5 % drop-out rate), will have 90 % power to detect a 40 % relative reduction (absolute reduction of 4 %) in admission to NICU from 10–6 % with two-sided alpha of 0.05.

Should this study show that dextrose gel is effective at preventing NICU admission, it will be critical to find out if this also improves long-term outcomes for babies. A sample size of 2,014 babies would allow us to detect a reduction in the number of children with one or more low developmental scores (<1SD below the mean) on a Bayley Infant Scales of Development Edition III assessment at 2 years from 40–33 %.

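### The sample size drops babies with an undetermined outcome, but the primary analysis counts them as NICU admissions in both arms, so the stated 90% power does not follow from the stated rule

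*Protocol article*

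**What the plan says.** Two sections of the protocol article bear on this point.

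- *Data analysis* sets an intention-to-treat logistic regression for NICU admission. A baby who dies, or "for whom the primary outcome of NICU admission cannot be determined will be assigned the worst case outcome of NICU admission", counts as an event. The rule makes no distinction by arm. Testing is at the usual level: "All tests will be two-tailed, with P < 0.05 considered significant".
- *Power and sample size* takes as its control rate that "10 % of at-risk babies will require admission to NICU". It then states: "A trial of 2,129 babies (1,014 in each arm, with continuity correction and allowing for 5 % drop-out rate"). This trial "will have 90 % power to detect a 40 % relative reduction (absolute reduction of 4 %) in admission to NICU", from 10% to 6%, "with two-sided alpha of 0.05".

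Drop-out is not defined. The 5% is attached to the NICU calculation both there and in the abstract. The two-year developmental target is a separate figure (2,014 babies).

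**The concern.** Raising a sample size for drop-out assumes that drop-outs contribute nothing and that the remaining babies keep the design rates. The analysis rule does the opposite. It keeps the babies with unknown status and gives each of them the event. The same block of events is added to both arms, which narrows the risk difference slightly, raises the variance and pulls the relative risk towards 1.

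The name given to the rule also misleads. Assigning the event may be the worst result for an individual baby. It is not the worst result for the comparison, because it goes to both arms and so bounds nothing.

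At stake are the power and the size of the primary effect estimate. If unknown outcomes are unevenly spread between arms, the direction of the bias is also at stake.

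**Working it through.** **Inputs.** From *Power and sample size*: 10% v 6%, two-sided alpha 0.05, 90% power, 1,014 per arm with continuity correction, 5% drop-out, 2,129 in total (1,064.5 per arm). From *Data analysis*: an undetermined outcome counts as an admission in either arm. Assumption: a fraction m of each arm is undetermined, unrelated to the true outcome. Centre stratification is not modelled because no centre rates are given.

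**1. The plan's own figure.** With p̄ = 0.08,

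n = [1.96√(2p̄(1−p̄)) + 1.2816√(p₁(1−p₁) + p₂(1−p₂))]² / (p₁−p₂)² = 964.6, so 965 per arm.

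Continuity correction: n/4 × [1 + √(1 + 4/(n × 0.04))]² = 1,013.99, so 1,014 per arm, as stated. Then 2 × 1,014 × 1.05 = 2,129.4, which matches 2,129.

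If 5% are left out, 1,064.5 × 0.95 ≈ 1,011 per arm remain at 10% v 6%. Power is 91.3%, or 89.9% with continuity correction. The stated 90% belongs to this analysis.

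**2. Rates under the rule.** q = p(1−m) + m. At m = 0.05:

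- placebo: 0.10 × 0.95 + 0.05 = 0.145
- dextrose: 0.06 × 0.95 + 0.05 = 0.107
- difference 0.038; relative risk 0.107/0.145 = 0.74 (design value 0.60)

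Each arm has 1,064.5 × 0.05 ≈ 53 imputed admissions. At the design rates about 48 of these (placebo, 90%) and 50 (dextrose, 94%) would be false.

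**3. Power under the rule.** With q̄ = 0.126 and n = 1,064.5,

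power = Φ{[|q₁−q₂| − 1.96√(2q̄(1−q̄)/n)] / √([q₁(1−q₁) + q₂(1−q₂)]/n)} = Φ[(0.038 − 0.02819)/0.01436] = Φ(0.683) = 75.3%.

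With continuity correction it is 73.2%. Simulation with 200,000 replicates gave 75.4% (chi-square), 73.4% (continuity-corrected) and 75.1% (Wald test of the log odds ratio).

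**4. Dependence on the undetermined fraction (2,129 babies).**

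| m per arm | Placebo v dextrose | Power | With continuity correction |
|---|---|---|---|
| 0 | 10% v 6% | 92.6% | 91.4% |
| 0.5% | 10.45% v 6.47% | 91.0% | 89.7% |
| 1% | 10.9% v 6.94% | 89.4% | 87.9% |
| 2% | 11.8% v 7.88% | 86.0% | 84.3% |
| 3% | 12.7% v 8.82% | 82.4% | 80.5% |
| 5% | 14.5% v 10.7% | 75.3% | 73.2% |

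Holding 90% under the rule at m = 5% would take about 1,653 per arm, or 3,306 in total, with continuity correction.

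**5. Type I error and bias.** With no true effect and equal missingness, both arms have the same rate (14.5% at m = 5%), so the type I error stays nominal. Unequal missingness changes this. The splits below are illustrative and do not come from the documents.

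- No true effect, 1.2% v 0.8% missing: 11.08% v 10.72%; false-positive rate about 6%.
- No true effect, 6% v 4% missing: 15.4% v 13.6%; false-positive rate about 22%.
- True 10% v 6%, with 6% missing on dextrose and 4% on placebo: 13.6% v 11.64%. The 4-point effect shrinks to about 2 points.
- The reverse split: 15.4% v 9.76%. The effect grows to 5.64 points.

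**The case against.** The strongest reply is that few outcomes will be unknown. Babies are randomised straight after birth and monitored in hospital. NICU admission and its length are recorded on a clinical form for the economic evaluation. Families are contacted on day 3 if already home, and again at 6 weeks. Stopping the gel does not make an outcome undetermined, because *Discontinuation of randomised treatment* keeps such babies in follow-up and analysis. Undetermined NICU status is narrower than the undefined 5% drop-out. There is also some slack: power is 92.6% with every outcome known and 91.0% at 0.5% unknown, both without continuity correction. All of this stands, and it limits the practical impact. It does not reconcile the two sections, since the plan attaches its 5% to this very outcome. If almost nothing will be missing, the rule also gains almost nothing.

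A second reply is that the rule is prespecified, treats the arms alike and errs towards no effect. That is right under equal missingness, so a reader who inferred a general inflation of false positives would be going too far. The 22% figure needs both high missingness and a 6% v 4% split that the documents do not give. Identical-looking gels in identically labelled syringes make such a split less likely.

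A third reply is that sensitivity analyses for missing data commonly sit in the statistical analysis plan, which is not shown. That is accepted: their absence from the article is no part of this point.

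**Conclusion.** The point holds as an inconsistency between two stated parts of the protocol. The 90% power belongs to an analysis that leaves undetermined babies out, whereas the protocol specifies one that counts them as admissions in both arms.

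The fall to about 75% (73% with continuity correction) rests on one assumption: that the 5% drop-out means an undetermined primary outcome, equal in both arms and unrelated to the true outcome. A reader might infer that the trial really has only 75% power. The documents do not support that, because they give no rate of unknown NICU status and their follow-up suggests a low one. At 1% the loss against the stated 90% is slight.

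Unequal missingness could bias the comparison in either direction, but its size here is illustrative only. The point should be fixed. It does not by itself undermine the trial.

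**What to change.** In *Data analysis*, define the primary analysis as all randomised babies with known NICU status, analysed as allocated, with deaths still counted as events. This agrees with the sample size as calculated, so 2,129 stands. Multiple imputation under missing-at-random is an optional addition and would change little if few outcomes are unknown.

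Move the rule that counts every unknown as an admission to a sensitivity analysis. Beside it, place two one-arm-only versions: unknowns counted as admissions on dextrose only, and on placebo only. These give real bounds on the comparison.

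If the present rule is kept as primary, restate the power in *Power and sample size* to match it, with the undetermined fraction that it assumes.

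The cost is one sentence of wording and a little more analysis work. No extra babies are needed and no trial procedure changes.

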### Economic evaluation

The cost-effectiveness of oral dextrose gel to prevent neonatal hypoglycaemia will be compared with usual care (no prophylaxis) within the period to discharge.

Intervention costs: A per-baby cost of dextrose gel will be based on the cost of the gel syringes and dispensing costs. For the no prophylaxis option, a zero intervention cost will be assumed.

Other Hospital Costs: Resource utilisation will be obtained from a clinical record form identifying both length of stay (LOS) and relevant Diagnostic Related Group (DRG) code for the mother, plus any subsequent operative procedure (DRG), respiratory problem requiring treatment (DRG), and NICU admission for the baby (plus LOS). Costs will be assessed using New Zealand Ministry of Health cost weights and purchase unit prices. For the no prophylaxis option, the costs from the placebo gel arm will be used.

Cost-effectiveness will be assessed using incremental cost-effectiveness ratios (ICERs) formed in terms of an incremental cost per case of hypoglycaemia avoided. Uncertainty in these figures will be assessed using non-parametric bootstrapping (sampling with replacement) to form a distribution for the ICER, potentially including corrections for any differences in the composition of the trial arms in any confounding factors. This analysis will be presented using cost-effectiveness acceptability curves that identify the likelihood of each option being cost-effective for different values attached to reducing a case of hypoglycaemia.

### Power and sample size

Based on data from Auckland City Hospital and Waikato Hospital, 10 % of at-risk babies will require admission to NICU. A trial of 2,129 babies (1,014 in each arm, with continuity correction and allowing for 5 % drop-out rate), will have 90 % power to detect a 40 % relative reduction (absolute reduction of 4 %) in admission to NICU from 10–6 % with two-sided alpha of 0.05.

Should this study show that dextrose gel is effective at preventing NICU admission, it will be critical to find out if this also improves long-term outcomes for babies. A sample size of 2,014 babies would allow us to detect a reduction in the number of children with one or more low developmental scores (<1SD below the mean) on a Bayley Infant Scales of Development Edition III assessment at 2 years from 40–33 %.

## Discussion

This study is the first to investigate whether neonatal hypoglycaemia and admission to NICU can be prevented by oral dextrose gel, a simple, cheap and painless intervention. This intervention requires no special expertise or equipment and hence is applicable in almost any birth setting. Reduction of admission to NICU will reduce separation of mother and baby, and may improve breastfeeding rates and reduce financial cost.

## Abbreviations

CI: Confidence interval
DRG: Diagnostic related group
hPOD: Hypoglycaemia Prevention in newborns with Oral dextrose
ICER: Incremental cost-effectiveness ratio
LOS: Length of stay
NICU: Neonatal intensive care unit
NHI: National health identifier
P: *P*-value
Pre-hPOD: Pre-hypoglycaemia Prevention in newborns with Oral Dextrose/dosage trial
SCBU: Special care baby unit
SD: Standard deviation
